### 2.2. Combined cilostazol-aspirin therapy in patients with ischemic stroke

Cilostazol, developed in Japan, significantly inhibited ischemic stroke recurrence and did not increase serious bleeding in a double-blind placebo-controlled study in patients with ischemic stroke (CSPS, Cilostazol Stroke Prevention Study). Similarly, cilostazol significantly inhibited strokes (ischemic stroke, intracerebral

hemorrhage, and subarachnoid hemorrhage) and reduced serious bleeding to half in a double-blind controlled study with aspirin (CSPS 2, Cilostazol Stroke Prevention Study 2).

The combination therapy of aspirin and cilostazol in patients with ischemic stroke has been tested in three small-scale studies, and no studies demonstrated any significant increase compared with aspirin monotherapy in serious bleeding complications. Summaries of the three studies are presented below.

In the TOSS study (Trial of Cilostazol in Symptomatic Intracranial Arterial Stenosis) examining the inhibitory effects of aspirin or combined aspirin-cilostazol therapy on stenosis progression in patients with intracranial arterial stenosis, combined aspirin-cilostazol therapy significantly inhibited progression of stenosis compared to aspirin monotherapy. There was no increase in intracerebral hemorrhage due to the combination therapy, and results suggested effectiveness and safety of combined aspirin and cilostazol. However, the observation period in this study was only 6 months.

The subsequent TOSS 2 study (Trial of Cilostazol in Symptomatic Intracranial Arterial Stenosis) examined the inhibitory effects of combined aspirin and clopidogrel versus aspirin and cilostazol on stenosis progression in patients with intracranial arterial stenosis. The study failed to demonstrate significant inhibition of stenosis progression, but serious bleeding was less frequent (0.9%) in the aspirin and cilostazol group compared to the aspirin and clopidogrel group (2.6%).

The CATHARSIS study (Cilostazol-Aspirin Therapy Against Recurrent Stroke with Intracranial artery Stenosis) followed stenosis progression and stroke recurrence in an aspirin monotherapy group and an aspirin-cilostazol combination group in patients with intracranial arterial stenosis for 2 years. No significant differences were observed in intracranial artery stenosis progression, perhaps due to a background factor bias. However, strokes were less frequent in the aspirin-cilostazol combination group (2.5%/year) than the aspirin monotherapy group (4.5%/year), and there was no increase in serious bleeding in the combination group compared to the monotherapy group. This set of results has demonstrated that combination therapy using cilostazol is superior in safety compared with conventional dual antiplatelet therapy.

## **2.2. Dual antiplatelet therapy using cilostazol in patients with cardiovascular disease**

With regard to cardiovascular diseases other than strokes, an overseas study has reported that the combination of cilostazol and other antiplatelet drugs does not increase bleeding complications.

A crossover study examining the effects of various combination therapies utilizing 3 antiplatelet drugs on bleeding time in patients with peripheral arterial disease showed a significant prolongation of bleeding time with the aspirin-clopidogrel combination compared to monotherapy with each drug. However, no significant prolongation of bleeding time was observed with cilostazol in combination with either aspirin or clopidogrel. Moreover, no prolongation of bleeding time was observed when cilostazol was added to the aspirin-clopidogrel combination therapy.

The CASTLE study (Cilostazol: A Study in Long-term Effects) was conducted with the primary objective of evaluating safety in patients with peripheral arterial disease. The effects of cilostazol and placebo were compared in 1,439 patients for a mean observation period of about 1.5 years. About 70% of patients used aspirin and about 27% used clopidogrel concomitantly in both placebo and cilostazol groups, but no

difference was observed in serious bleeding events between the two groups.

A meta-analysis examined prophylactic effects on stenosis recurrence and safety following drug-eluting stent implantation in patients with coronary artery disease. No significant difference in bleeding events or serious bleeding events was observed between groups receiving either aspirin and clopidogrel or a 3-drug combination with cilostazol added.

These reports suggest that the adding either aspirin or clopidogrel to cilostazol use does not increase risk of bleeding complications.

Based on these clinical results, the current study will examine prophylactic efficacy on ischemic stroke recurrence between SAPT group and DAPT group with cilostazol added to conventional antiplatelet therapy in high risk patients with at least two risk factors of intracranial arterial stenosis, carotid stenosis, or ischemic stroke, with observation period at least one year.

### 3. Patient Selection

#### 3.1. Target disease

Noncardioembolic ischemic stroke

#### 3.2. Inclusion criteria

Patients meeting all of the following criteria will be included:

- 1) Patients with a diagnosis of noncardioembolic ischemic stroke that developed between 8 and 180 days before the first day of observation
- 2) Patients with a responsible lesion identified by head MRI
- 3) Patients 20 to 85 years of age when providing informed consent
- 4) Patients taking aspirin or clopidogrel alone as antiplatelet therapy when providing informed consent
- 5) Patients meeting at least one of the following criteria:
  - i. At least 50% stenosis of a major intracranial artery (to the level of A2, M2, P2)
  - ii. At least 50% stenosis of an extracranial artery\*
 

\* common carotid artery, internal carotid artery, vertebral artery, brachiocephalic artery, or subclavian artery
  - iii. Two or more of the following risk factors:
    - 65 years of age or older
    - Diabetes mellitus
    - Hypertension
    - Peripheral arterial disease
    - Chronic kidney disease
    - History of symptomatic ischemic stroke (excluding the index IS for this study)
    - History of ischemic heart disease
    - Smoking (only current smokers, excluding previous smokers)
- 6) Patients able to visit the study center throughout the observation period

7) Patients who provided written informed consent for participation

#### *Rationale for inclusion criteria*

- 1) A minimum of 8 days after onset was set because symptoms should be stable to a certain extent, and a maximum of 180 days after onset was set because recurrence rate decreases gradually over time.
- 2) To confirm the diagnosis of ischemic stroke
- 3) A minimum age of 20 years was set because that is required for valid consent, and a maximum age of 85 years was set because of the length of the observation period.
- 4) Patients taking aspirin or clopidogrel alone when providing informed consent were considered suitable based on the study design.
- 5) The following criteria were established to determine high risk of stroke recurrence:
  - i. Based on the WASID trial sub-analysis report
  - ii. Based on the ACSRS study sub-analysis report
  - iii. Based on the Stroke Prevention Model, the Fukuoka Stroke Risk Score and the CAPRIE trial sub-analysis.
- 6) Established in order for the patients to be able to undergo planned observation and tests.
- 7) Complied with the “Ethical Guideline for Clinical Studies.”

### **3.3. Exclusion Criteria**

Patients meeting any of the following criteria will be excluded:

- 1) Patients with emboligenic heart disease (See 29. *References*)
- 2) Patients taking any anticoagulant agents
- 3) Patients who cannot undergo MRI examination for reasons such as claustrophobia or implanted pacemaker
- 4) Patients scheduled to undergo any surgery during the study period, including percutaneous angioplasty, stent placement, or bypass grafting
- 5) Patients with a drug-eluting coronary stent implanted within the past year
- 6) Patients with a history of symptomatic non-traumatic intracranial hemorrhage, any other hemorrhagic disease (e.g. active peptic ulcer), bleeding predisposition, or blood clotting disorders
- 7) Patients with a history of hypersensitivity to cilostazol
- 8) Patients with congestive heart failure or uncontrolled angina pectoris
- 9) Patients with thrombocytopenia (platelet count  $\leq 100,000/\text{mm}^3$ )
- 10) Patients with severe liver or renal dysfunction (See 29. *References*)
- 11) Women who are pregnant, breast-feeding, or of child-bearing potential
- 12) Patients with malignant tumor requiring treatment
- 13) Patients who are taking aspirin and meet any of the following criteria:
  - History of hypersensitivity to aspirin or salicylic acid analogues
  - Peptic ulcer complication
  - Aspirin-induced asthma or its history

- 14) Patients who are taking clopidogrel, and meet the following criterion:
  - History of hypersensitivity to clopidogrel
- 15) Patients who are participating in any other clinical studies
- 16) Patients considered by the investigator/subinvestigator to be unsuitable for this study

#### *Rationale for exclusion criteria*

- 1) To eliminate risk of enrolling patients with cardioembolic ischemic stroke
- 2) Anticoagulant agents are specified as prohibited concomitant medications
- 3) Prevents specified examinations
- 4) Evaluation will be strongly affected by these surgeries
- 5) Dual antiplatelet therapy is necessary for one year after the drug-eluting stent implantation
- 6) to 16) To secure the safety of study subjects based on the precautions for using cilostazol, aspirin, and clopidogrel

## **4. Enrollment and Allocation**

### **4.1. Enrollment and allocation**

The investigator/subinvestigator must obtain written informed consent from all patients prior to study enrollment. After obtaining written informed consent, the investigator/subinvestigator must assign a uniformly-determined subject identification code (see *14.6 Privacy protections and subject identification*) and enroll the subject through the Internet enrollment system. After enrollment, the investigator/subinvestigator must find out which treatment group the subject was allocated to from the enrollment system. For details, refer to the *Subject enrollment manual*.

The following items must be input into the system when subjects are enrolled:

- Subject identification code
- Date of written informed consent
- Sex
- Date of birth
- Date of most recent noncardioembolic IS
- Eligibility information (confirmation of inclusion and exclusion criteria)
- Scheduled date of first visit

### **4.2. Allocation methodology**

The enrollment center will allocate subjects to treatment groups using blocked randomization according to study center.

## **5. Treatment plan and criteria for changes in dosage or schedule**

### **5.1. Protocol treatment**

#### **5.1.1. Dosage and administration**

SAPT group

One of the following drugs will be administered:

|              |                               |
|--------------|-------------------------------|
| Aspirin:     | 81 or 100 mg/day (once daily) |
| Clopidogrel: | 50 or 75 mg/day (once daily)  |

#### **DAPT group**

One of the following drugs will be administered:

|              |                               |
|--------------|-------------------------------|
| Aspirin:     | 81 or 100 mg/day (once daily) |
| Clopidogrel: | 50 or 75 mg/day (once daily)  |

As a rule, cilostazol (Pletaal OD tablet® & reg.) will be co-administered twice daily at the maintenance dose of 200 mg/day. However, the starting dose can be 100 mg/day, in which case the dose must fundamentally be increased to 200 mg/day within 15 days.

Cilostazol, aspirin and clopidogrel are referred to below as study drugs.

#### **5.1.2. Treatment initiation timing**

Treatment with cilostazol will be initiated on the first day of observation.

Type or dosage of aspirin or clopidogrel will not be changed after obtaining written informed consent.

#### **5.1.3. Confirming treatment status**

The investigator/subinvestigator must confirm subject's treatment status by interview and record it on his/her medical record.

### **5.2. Criteria for changes in dosage or treatment schedule**

Dosage or treatment schedule of aspirin or clopidogrel will fundamentally not be changed during the observation period.

If a headache etc. occurs after treatment with cilostazol at a dose of 200 mg/day, the treatment will continue at a reduced dosage of 100 mg/day.

Study drug may be withdrawn in event of surgery or other invasive procedures, but the period of drug withdrawal may not last more than 4 weeks.

### **5.3. Criteria for subject discontinuation or completion**

If it is determined that continued observation of a subject is impossible due to the following reasons, that subject will be withdrawn from the study and the reason and date for this recorded. All necessary observations and tests will be performed at this time, and efficacy and safety evaluations performed.

- 1) Subject requests discontinuation or withdraws consent
- 2) A serious adverse event occurs which makes continuation problematic
- 3) Any event described in 6.3.3. occurs

- 4) Drug withdrawal lasts longer than 4 weeks
- 5) Any other reasons which lead the investigator/subinvestigator to consider continued participation problematic

Observation will also be discontinued for patients who discontinued taking study drugs.

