| Head MRI (T2* WI)                            | ← △ →           |             |                       |           |         |         |          |                            |                         |
| Head MRA                                     | ← △ →           |             |                       |           |         |         |          |                            |                         |
| Carotid artery imaging                       | ← △ →           |             |                       |           |         |         |          |                            |                         |
| Laboratory test (blood)                      | ← ○ →           |             |                       | ← ..... → |         |         |          |                            |                         |
| Laboratory test (urine)                      | ← ○ →           |             |                       | ← ..... → |         |         |          |                            |                         |
| Chest x-ray                                  | ← ○ →           |             |                       | ← ..... → |         |         |          |                            |                         |
| ECG                                          | ← ○ →           |             |                       | ← ..... → |         |         |          |                            |                         |
| Adverse events                               |                 |             | ← ..... →             |           |         |         |          |                            |                         |

○ Required item △ Optional item <.....> As required

\* Observation is complete when a subject meets criteria for discontinuation/completion, or when 1 year has elapsed from initiation of observation for last subject enrolled.

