#### Other vascular events\*

Date and details

\* e.g. aortic dissection or rupture; pulmonary embolism; heart failure, angina pectoris, or occlusive arteriosclerosis requiring hospitalization; and revascularization of coronary artery, aorta, peripheral artery, etc.

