### **6.2.5 Evaluated events**

The number of days from the first day of observations until onset (date of evaluated event onset - observation start date) will be calculated for the following evaluated events.

Death, ischemic stroke, intracerebral hemorrhage, subarachnoid hemorrhage, transient ischemic attack (TIA), myocardial infarction, other vascular events [aortic dissection or rupture; pulmonary thrombosis; heart failure, angina pectoris, or occlusive arteriosclerosis requiring hospitalization; revascularization (e.g., coronary artery, aorta, peripheral artery)]

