## 7. DISPOSITION OF PATIENTS

The follow data summaries will be prepared for all subjects allocated to a treatment (ITT).

For the subjects for whom observations are discontinued or completed, the numbers of subjects observed for 1 year and 2 years and frequency distributions of the reasons for discontinuation/completion will be determined for each treatment group.

Discontinuation of observations: When the following criteria for discontinuation/completion are met and observations are discontinued.

Discontinuation/completion criteria

- 1) The subject requests that their study participation be discontinued or withdraws their consent

- 2) A serious adverse events occurs, making continued study participation difficult
- 3) An evaluated event occurs
- 4) The study drug is continuously withdrawn for more than 4 weeks
- 5) The investigator/subinvestigator otherwise determines that the subject's continued study participation would be difficult

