## **9.2 Secondary endpoints**

The secondary endpoints will be those indicated below. Events or accidents that occur between the observation start date and the observation end date (during the observation period) will be included in the analysis.

1. Stroke (ischemic stroke, intracerebral hemorrhage, subarachnoid hemorrhage)
2. Intracerebral hemorrhage or subarachnoid hemorrhage
3. Ischemic cerebrovascular disorder (ischemic stroke, TIA)
4. Death from any cause
5. Stroke (ischemic stroke, intracerebral hemorrhage, subarachnoid hemorrhage), myocardial infarction, or vascular death
6. All vascular events: stroke, myocardial infarction, and other vascular events [e.g., aortic dissection or rupture; pulmonary embolism; heart failure, angina pectoris, or occlusive arteriosclerosis requiring hospitalization; and revascularization (e.g., coronary artery, aorta, peripheral artery)]

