### **9.2.4 Death from any cause**

All deaths will be included in the analysis.

Subjects discontinued for reasons other than death, which will be included in the analysis, and subjects who continue to study completion will be considered censored subjects. The censor date will be considered the observation completion date.

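### Observation stops at the first listed event of any kind, so deaths after a non-fatal event are censored from all-cause death, and other endpoints are cut short by events that are not their components

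*Supplement*

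**What the plan says.** Protocol v1.3, section 5.3, opens with "If it is determined that continued observation of a subject is impossible due to the following reasons" and gives as its third reason "Any event described in 6.3.3. occurs". Section 6.3.3 lists death, ischaemic stroke (IS), ICH, SAH, TIA, MI and other vascular events. The last group includes "heart failure, angina pectoris, or occlusive arteriosclerosis requiring hospitalization; and revascularization of coronary artery, aorta, peripheral artery, etc". The footnote to the schedule in 6.1 carries no such condition: "Observation is complete when a subject meets criteria for discontinuation/completion".

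The SAP follows the same rule:
- Section 7 gives "An evaluated event occurs" as a discontinuation criterion. Section 6.2.5 defines evaluated events as "Death, ischemic stroke, intracerebral hemorrhage, subarachnoid hemorrhage, transient ischemic attack (TIA), myocardial infarction, other vascular events", with the same cardiac and revascularisation items.
- Section 6.2.4 sets the last observation day as the day a criterion is met.
- Section 9.1 analyses the first IS within that window and censors anyone discontinued for another reason.
- Section 9.2 restricts the secondary endpoints to "Events or accidents that occur between the observation start date and the observation end date", and 9.2.1 to 9.2.6 censor in the same way.
- Section 9.2.4, on all-cause death, says "All deaths will be included in the analysis".

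Neither document plans vital-status or endpoint follow-up after a first non-fatal event. Protocol section 25 follows only unrecovered or drug-related adverse events. The SAP plans no competing-risk or sensitivity analysis for this.

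**The concern.** As written, the mortality endpoint measures death with no preceding listed event. It leaves out deaths that follow a stroke, which are the deaths that stroke prevention could avert. SAPT patients are expected to have more strokes, so they leave the mortality risk set more often, and a mortality benefit acting through fewer strokes would be hidden.

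The same rule reaches the other endpoints to different degrees:
- Primary endpoint: an IS after a TIA, MI, angina admission or revascularisation is not counted.
- ICH or SAH: cut by any ischaemic or cardiac event.
- Any stroke, and stroke/MI/vascular death: cut by TIA and other vascular events. Any stroke is also cut by MI.
- IS or TIA: cut by haemorrhage, MI and other vascular events.
- All vascular events: among non-fatal events, cut only by TIA, since the others are its components.

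This sits poorly with an analysis set labelled ITT. Outcomes that were never collected cannot be recovered after database lock.

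**Working it through.** **1. The plan's own figure.** Inputs from Protocol 11.1: rates 4% and 2.8% a year, 2.5 years' enrolment, 3.5 years' maximum observation, two-sided 5%, power 80%.

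Events = 4(1.960 + 0.842)² / (ln 0.70)² = 247. With exponential hazards 0.04 and 0.028, follow-up uniform on 1 to 3.5 years and no dropout, the event probabilities are 0.0857 and 0.0609, mean 0.0733. Then 247 / 0.0733 / 2 gives about 1,686 per group, against 1,688 stated. The step to 2,000 implies 1 − 1,688/2,000 = 15.6% loss. Five per cent a year over 3.5 years is 1 − 0.95^3.5 = 16.4%. The sample size reproduces. It has no term for truncation by other events.

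**2. Deaths lost.** Inputs from the documents: IS hazard λ = 0.04 (SAPT) and 0.028 (DAPT); dropout d = −ln 0.95 = 0.0513; 2,000 per group; v1.3 calendar (Protocol 10.2: enrolment October 2013 to March 2017, end March 2018), so potential follow-up T is uniform on 1 to 4.5 years. Assumed: mortality m of 1% a year before a stroke and km after it, no early fatality, and no other listed event.

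- Counted: A(T) = m/h × (1 − e^(−hT)), with h = m + λ + d.
- Uncounted: B(T) = ∫₀ᵀ λ e^(−ht) × km/(km + d) × (1 − e^(−(km+d)(T−t))) dt.
- Average both over T and multiply by 2,000. Share lost = B/(A + B).

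| Mortality after stroke | Arm | Counted | Uncounted | Share lost |
|---|---|---|---|---|
| Unchanged (k = 1) | SAPT | 47.2 | 2.9 | 5.7% |
| | DAPT | 48.1 | 2.0 | 4.1% |
| Tripled (k = 3) | SAPT | 47.2 | 8.4 | 15% |
| | DAPT | 48.1 | 6.0 | 11% |

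Overall: (2.9 + 2.0)/100.2 = 4.9% at k = 1, and (8.4 + 6.0)/109.7 = 13.1% at k = 3. With m = 2% the overall shares are 4.9% and 12.8%.

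The k = 3 rows show what is hidden. All deaths are 47.2 + 8.4 = 55.6 in SAPT and 48.1 + 6.0 = 54.1 in DAPT. The counted deaths come from the same hazard m in both arms, so the planned analysis would show no difference by construction.

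Adding other listed events at an assumed 1 to 3% a year, on the shorter 2.5/3.5-year timing with m of 1 to 2%, gives 5 to 7% lost if mortality is unchanged after an event, 9 to 14% if doubled and 14 to 19% if tripled.

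**3. Primary endpoint.** Power = Φ(½√D × |ln 0.70| − 1.960), with 2,000 per group, 5% yearly dropout, 2.5/3.5-year timing and truncation by non-IS events at an assumed rate c.

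| c per year | Events D | Power |
|---|---|---|
| 0 | 275.6 | 84.2% |
| 1% | 272.4 | 83.7% |
| 3% | 266.1 | 82.9% |
| 5% | 260.0 | 82.0% |

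The fall is about 0.4 to 2.2 points. On the v1.3 calendar, power goes from 89.8% (c = 0) to 87.6% (c = 5%).

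**The case against.** Four points can be made for the plan.

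*The rule is discretionary.* The preamble to 5.3 applies when continued observation is judged impossible, which a TIA seldom makes it. SAP 7 also speaks of criteria being met and observation being discontinued. This stands as far as 5.3 itself goes. The 6.1 footnote and SAP 6.2.4 leave no discretion, so the passages conflict.

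*Early deaths may be counted.* Death is itself a 6.3.3 event, the adverse event outcome record takes a date of death, unrecovered events are investigated within 4 weeks, and SAP 9.2.4 says all deaths count. This stands in part. Whether a death days after a stroke is analysed is an unresolved conflict between SAP 9.2.4 and SAP 6.2.4 and 9.2, so its loss is not established. A reader might infer that 24 to 62% of deaths go uncounted. That range needs assumed listed-event rates of 6% and 4.5% a year, 3 to 10% early fatality that is always excluded, and 2 to 4% yearly mortality afterwards. About half or more of the loss is early deaths (14.6 of 29 at the low end, 49 of 75 at the high end). Without them the share is about 12 to 21%. The documents support none of these rates.

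*The primary test is sound.* This largely stands. A reader might infer a biased primary hazard ratio because censoring at TIA is probably informative. But events lost in both arms do not by themselves shift the ratio, and the documents give no rate from which a bias could be calculated.

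*All-cause death is one of six secondary endpoints without multiplicity control.* True, and it limits the severity. The endpoint would still not measure what its name says.

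**Conclusion.** The point holds and should be fixed. It is chiefly a fault in how all-cause death is defined, with lesser effects on the other secondary endpoints and a small effect on the primary. The text alone establishes three things: the SAP conflicts with itself on which deaths count; the protocol conflicts with itself on whether a listed event must end observation; and the resulting censoring is related to treatment under the trial's own hypothesis.

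The size rests on assumed mortality. About 5% of deaths lost is the result with the protocol's stroke rates and no excess mortality after stroke, and about 13% if mortality triples. The loss is larger if other listed events are added or if early deaths are also excluded. In every scenario examined, proportionally more deaths are lost in SAPT. The sample size is not in error, and primary power stays above 80% over the range examined.

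**What to change.** Separate the end of protocol treatment from the end of observation, and reconcile Protocol 5.3 and the 6.1 footnote with SAP 6.2.4, 7 and 9.

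- State that neither a non-fatal 6.3.3 event nor a later stop of study drug after it ends outcome follow-up. The second part is needed because 5.3 also ends observation when study drug is stopped; removing the third criterion alone would leave many of these patients censored.
- After such an event, continue to record vital status with cause of death, and later IS, ICH, SAH and MI, on the existing 6-monthly schedule to the common study end.
- Analyse each endpoint as time to the first component of that endpoint. Censor at study end, loss to follow-up, withdrawal of consent, or death where death is not a component.
- Keep the SAP's time origin (observation start) unless a change is separately justified.

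This concerns data collection and analysis only. Treatment after an event stays with the existing clinical rules.

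Cost: a protocol and SAP amendment with ethics review, possible re-consent, continued status checks in the minority with an event, and committee evaluation of some additional events.
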